**Aims/objectives**

This study aims to identify:

- If self-reported measures of stress, life satisfaction, and resilience, improve after 10 and 30 days of a mindfulness-based app (Headspace) intervention, relative to a wait-list control group.

- If there is a linear or non-linear change in scores between baseline, day 10, and day 30 in the experimental condition.

- If those who experience the largest reductions in stress also experience the largest increases in resilience.

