**Hypotheses**

H1: The control group will have significantly worse scores on all measures at day 10 and day 30 day compared to the experimental (Headspace) group.

H2: There will be a greater positive impact on study outcomes following 30 days of Headspace use relative to 10 days.

H3: Those who experience larger reductions in stress across 30 days of the Headspace intervention will also experience larger increases in resilience over the same time period.

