**Research Methodology**

This study will use a repeated-measures, between-group, randomised controlled design.

Participants will only be selected if they indicate good general health, no prior experience with mindfulness practice, and no recent adverse life events, as assessed via an initial screening tool. Those who meet inclusion criteria and respond within the recommended time period of two weeks will be directed to a webpage, via the Survey Monkey platform, and a detailed participant information sheet. Participants will be informed that they will be randomly assigned either to an experimental group or to a ‘wait-list’ control group, and will be asked to provide informed consent before completing a brief demographics questionnaire. Participants will then be randomly allocated to the Headspace intervention or to a control group. The control group will be informed that they are a ‘wait-list’ group, and will be required to complete questionnaire measures at baseline, and 10 and 30 days later, before being offered access to the Headspace intervention for a further 30 days (should they wish to use it). They will be given detailed instructions of how to download and use the Headspace intervention via their smartphone at the end of the wait-list period. The treatment group will be given instructions to complete questionnaire measures at baseline and then again at 10 and 30 days of the Headspace intervention. Following baseline measures, participants in the Headspace group will be given an access code and details of how to download the Headspace programme to their smartphone. Participants will be gently encouraged to use the app every day during the 30-day study period, and to retain a diary to record hours/days of activity/usage. Between days 9 and 10 of the Headspace intervention, participants in both groups will receive an email encouraging them to complete all outcome measures again via Survey Monkey. Another email reminder will be sent out within 24 hours of completing the full 30-day intervention. If no action is taken further emails will be sent within 5 days of completion. Participants in both groups will be reminded they have the right to withdraw at any point during the study.

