**Recruitment of Participants**

Opportunistic and snowball sampling will be applied via an email asking for volunteers from the general population to take part in a study on mindfulness and well-being (see Appendix for email copy). Those that respond within a two-week time period will be guided to a webpage on Survey Monkey, which will introduce the research and screening procedure. If the participant passes the screening tool, they will be randomly assigned to an experimental group or a control group. The target sample size is 60 participants in total. For those who do not meet inclusion/exclusion criteria, they will be immediately debriefed and further guidance provided.

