**Statistical Analysis**

Analysis will be carried out using repeated measures analysis of variance (ANOVA) with group (mindfulness vs control) and time as factors (baseline, day 10, day 30). Pearson’s correlational analysis will also be conducted to explore whether potential gains in well-being experienced by the experimental group are related to participants’ subjective ratings of task enjoyment and task difficulty. Post-hoc t-tests will also be conducted to assess mean score differences between the three time points in each group.

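### H1 is a between-group claim at day 10 and at day 30, but no stated test locates a group difference on either day: the ANOVA interaction is an overall test and the follow-up t-tests are within-group

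*Protocol*

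**What the plan says.** The hypothesis is comparative and tied to two days. In the protocol, H1 in the Hypotheses section reads as follows: "The control group will have significantly worse scores on all measures at day 10 and day 30 day compared to the experimental (Headspace) group". The first item under Aims/objectives asks, for each of the three outcomes, whether scores "improve after 10 and 30 days of a mindfulness-based app (Headspace) intervention, relative to a wait-list control group". The Research Methodology section fits this: "This study will use a repeated-measures, between-group, randomised controlled design".

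The Statistical Analysis section gives two relevant analyses. The main one is a "repeated measures analysis of variance (ANOVA) with group (mindfulness vs control) and time as factors (baseline, day 10, day 30"). The follow-up is "Post-hoc t-tests will also be conducted to assess mean score differences between the three time points in each group". The section does not say which ANOVA term decides H1, and it states no comparison of the two groups at day 10 or at day 30.

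The only design figure given is in Recruitment of Participants: "The target sample size is 60 participants in total".

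**The concern.** A 2 x 3 ANOVA offers two terms that involve group. The group main effect averages over all three time points, including baseline, where randomised groups should not differ. The group x time interaction asks whether the two profiles differ in shape anywhere. A significant interaction is compatible with an effect at day 10 only, at day 30 only, or at both, so it cannot by itself support a claim about each day.

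The natural next step is a follow-up test, and the protocol names one. It compares time points inside each arm. A reader who wants a day-10 conclusion then has only this to look at: did Headspace change significantly by day 10, and did control? A difference in significance between arms is not a test of the difference between arms. Each within-arm change also carries whatever both arms share, such as retest effects, regression to the mean or calendar effects. The day-specific half of H1, on all three outcomes, could then be judged on the wrong evidence.

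**Working it through.** **Side by side.** H1 needs 3 outcomes x 2 days = 6 between-group contrasts. The stated follow-up gives 3 pairs of time points x 2 groups x 3 outcomes = 18 within-group tests. None of the 18 is one of the 6.

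**Inputs.** From the protocol: 60 participants, two groups, three time points. The protocol gives no alpha, SD, correlation or allocation ratio. Assumed: 30 per arm, SD 1, two-sided 0.05, equal correlation between all time points, no dropout. There is no power calculation in the protocol to reproduce.

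**Step 1: does the ANOVA compare the groups?** Yes. In 20,000 simulated trials per scenario, the interaction test rejected in about 5% when there was no group difference. With a true 0.5 SD effect at day 30 only, it rejected in 49% (correlation 0.5) or 73% (0.7).

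**Step 2: does the ANOVA locate the day?** No. With a 0.8 SD effect at day 30 only and correlation 0.5, the interaction rejected in 89% of trials, while a direct between-group test at day 10 rejected in 5%, its nominal rate.

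**Step 3: within-group tests read alone, no app effect.** Let both arms change by 0.3 SD, with correlation 0.6.
- Standardised paired effect: 0.3 / sqrt(2 x (1 - 0.6)) = 0.3 / 0.894 = 0.335.
- Noncentrality: 0.335 x sqrt(30) = 1.84, which gives power p = 0.427 in each arm on a paired t-test with 29 df.
- Headspace significant and control not: p(1 - p) = 0.427 x 0.573 = 0.245.
- One arm significant and the other not, in either direction: 2 x 0.245 = 0.489.

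Over a shared change of 0.2 to 0.4 SD and correlation 0.6 to 0.7, the Headspace-only figure is 17% to 25%. A valid between-group test favours Headspace in about 2.5%.

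**Step 4: the same, behind a significant interaction.** With no app effect, a significant interaction together with the Headspace-only pattern occurred in about 2% of simulated trials. If the follow-up is read only after a significant interaction, the ANOVA protects against a false claim when the app does nothing at all.

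**Step 5: an effect on one day only.** Shared change of 0.3 SD at both follow-ups, app effect 0 at day 10 and 0.8 SD at day 30, correlation 0.6. The between-group test here compares change from baseline and counts results in favour of Headspace.

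| Quantity | Share of trials |
|---|---|
| Interaction significant | about 95% |
| Of those: Headspace-only pattern at day 10 (no true effect) | about 24% |
| Of those: between-group test positive at day 10 | about 3% |
| All trials: Headspace-only pattern at day 30 (true effect) | 57% |
| All trials: between-group test positive at day 30 | about 92% |

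Here the interaction is rightly significant, so it no longer protects the day-10 conclusion. The last two rows show the opposite error: at day 30 the within-group pattern often hides a real effect, because control also changes significantly.

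**The case against.** The strongest reply is that the randomised comparison is already planned. A reader might infer from the follow-up sentence that H1 goes untested, or that the trial gives up its randomised comparison. The document does not support that. Group is a factor in the main ANOVA, its interaction is a valid overall between-group test, and the t-tests are described as additional and post hoc. Nothing says that benefit will be inferred from one arm being significant and the other not. It would therefore be wrong to give 24% as the false-positive rate of the plan when the app has no effect: that figure needs the ANOVA to be ignored, and behind a significant interaction it falls to about 2%. This part of the reply stands.

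The within-group tests also have a proper use. The second aim concerns the course of scores over time in the experimental arm, and H2 compares 30 days of use with 10. A comparison of time points within the Headspace arm bears on both. This stands too, and it rules out deleting these tests or stripping their p-values.

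Finally, an analysis plan that is not shown might add day-specific contrasts. It might. But the protocol is not silent here: it names follow-up tests, and they answer a different question from H1. Even with the ANOVA as gatekeeper, Step 5 shows that the gap at the level of the day remains.

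**Conclusion.** The concern holds in a limited form. The overall group question is tested; the day-specific question that H1 and the first aim pose is not. The interaction cannot say on which day the groups differ, and the stated within-group tests cannot say it either. In the scenario with an effect at day 30 only, about 24% of trials with a significant interaction show a misleading day-10 pattern, against about 3% with a direct test.

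These sizes rest on assumed values (30 per arm, correlation 0.6, shared change 0.3 SD, effect 0.8 SD), since the protocol supplies none. The structural point, that none of the 18 stated tests is one of the 6 needed, depends on no assumption. It is worth correcting before the data are analysed.

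**What to change.** Amend the Statistical Analysis section along these lines:

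- The group x time interaction is the overall test of H1 for each outcome.
- For each outcome, the between-group difference at day 10 and at day 30, adjusted for baseline, will be estimated with a 95% confidence interval. These are the day-specific tests of H1.
- Multiplicity across the 3 outcomes x 2 days will be controlled, for example by Holm's procedure.
- Within-group comparisons of time points serve the second aim and H2 only and will not be used to judge H1.

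The multiplicity rule matters: six tests at 0.05, treated as independent, give a family-wise error of 1 - 0.95^6 = 26%.

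The cost is a few sentences and a little more analysis, with no new data. The rule also makes the thresholds stricter: Holm compares the smallest of six p-values with 0.05/6 = 0.0083. By the normal approximation with 30 per arm, the difference detectable with 80% power in a single unadjusted test is (1.96 + 0.84) x sqrt(2/30) = 0.72 SD at 0.05, and (2.64 + 0.84) x sqrt(2/30) = 0.90 SD at 0.0083. Baseline adjustment recovers much of this: at an assumed correlation of 0.6 it multiplies the detectable difference by sqrt(1 - 0.36) = 0.8, so 0.90 becomes 0.72 SD.

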**Appendix**
